## Abstract

**Background:**

Environmental toxins are particularly harmful to pregnant women and their fetuses due to the long-term effects of these toxins on children after birth. Environmental health behaviors can prevent and protect mothers and their babies’ environmental health.

**Methods/Design:**

This study presents a protocol for a double-blinded randomized controlled trial to examine the effect of a mobile application named “DECO-MOM” (Deep ECOlogy-MOM) for pregnant women. This application contains content related to environmental perceptions and behaviors according to the revised protection motivation theory. The mobile intervention will be implemented for 4 weeks for 40 pregnant women with a gestational age in the first trimester. As the control group, 40 pregnant women will be recruited at public healthcare centers in Chuncheon and Gongju in South Korea. The hypothesis is that the experimental group will have higher scores for environmental perceptions and behaviors than the control group. An online survey administered before and after the intervention will contain outcome parameters including depression, stress, quality of life, e-learning satisfaction, environmental perceptions, and environmental behaviors.

**Discussion:**

This study will elaborate a guide for an intervention to enhance the effects of the mobile application on strengthening environmental health perceptions, behaviors, e-learning satisfaction, and quality of life and curtailing depression and stress among pregnant women.

**Trial registration:**

Trial registration Number: KCT0007725, Registered September 22, 2022. Prospectively registered.

## Background

Environmental health is defined as the protection of the human body from environmental toxins such as air, climate, drinking water, chemicals, and radiation to maintain safety and wellness [1]. Environmental health hazards include exposure to substances, stimuli, or environmental conditions such as toxic substances and stressors. The characteristics of an exposure include the concentration, time, duration, frequency, and route of contact [2]. Pregnant women are a vulnerable population to environmental exposures because estrogen receptors are more widely distributed in the reproductive organs, breasts, and adipose tissue than before pregnancy. The placental tissues transfer environmental toxins to the fetus and affect the formation and growth of human organ systems, especially in the first trimester [3]. Climate change and air pollution exacerbate and induce health problems in pregnant women from micro-dust, ozone, and heavy metals [4].

Environmental toxicants such as endocrine disruptors (EDCs) affect pregnant women, fetuses, neonates, infants, and children throughout the lifespan. Correlations have been reported between lead in the water and a low birth rate [5] and between other chemicals with a low fertility rate [6]. Air pollution has been reported to show correlations with preterm birth and spontaneous abortion [7]. In fetuses, associations have been identified between phthalates and small for gestational age [8], between lead exposure and fetal death [5], and between EDCs and congenital anomalies [6]. In newborn babies, environmental pollutants have been reported to be correlated with low birth weight [5, 8–10]. In infants, impacts of environmental pollutants on atopic dermatitis, respiratory diseases, cognitive delays, attention deficit disorder, and sleep disturbances have been reported [10], as well as a correlation between phthalates and male reproductive disorders [11]. In children, correlations have been reported between phthalates and mental development delays [12], low weight, and low body mass index [8], as well as between electric wave exposure and cognitive delay [13].

Preventing environmental exposure and protecting the health of pregnant women and their babies are important for the health status of the next generation given the circumstances of climate change and environmental pollution [14]. Birth education about environmental health is the principal vehicle to convey information to pregnant women and their family members about health behaviors, and internet-based interventions are useful in the post-pandemic society [15]. Among various approaches to internet-based interventions, mobile applications are particularly feasible and accessible [16]. However, few studies have explored the possibility of promoting environmental health behaviors among pregnant women via a mobile application intervention, although one study was conducted on an intervention using online lectures and cartoon comics [17]. Hence, this study will be aimed to test the effectiveness of a mobile application intervention named “DECO-MOM” (Deep ECOlogy-MOM) for pregnant women. The hypothesis of this study is that this mobile application intervention for pregnant women will enhance their environmental perceptions and behaviors. Additionally, this study will test e-learning satisfaction, depression, stress, and quality of life as secondary outcomes.

## Methods

### Study design

This study will have a 1:1 parallel randomized controlled trial design. The researchers and participants will be double-blinded during the registration, allocation, intervention, and statistical analysis phases. Cluster sampling will be used with blocked randomization at two health centers. The intervention group and control group will be recruited from registration lists for birth education by two trained research assistants at health care centers using SPSS for Windows version 24.0 (IBM Corp., Armonk, NY, USA) to conduct randomization. Participants’ identities will be coded to ensure that they remain unknown to the researchers. The participants will be pregnant women in the first trimester who have no physical or psychological diseases. This study will receive approval from the institutional review board of Kongju National University, and the participants will complete written consent forms in face-to-face meetings with the researchers. This protocol was developed and documented in accordance with the Consolidated Standards of Reporting Trials (CONSORT) guidelines [18] and registered in the Korean Clinical Research Information Service [19]. The registration number (KCT0007725) can be retrieved from https://cris.nih.go.kr/cris/search/detailSearch.do?seq=22378&status=5&seq_group=22378&search_page=M (22/09/2022).

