### Allocation

In total, 40 participants (20 recruited from each of the two cities) will be allocated to the intervention group (mobile application plus usual prenatal class) and 40 participants (20 from each of the two cities) will be allocated to the control group (usual prenatal class only). If pregnant women agree to participate in the study, nurses at the centers will obtain their mobile phone numbers and refer them to the researcher. The researcher will contact the pregnant women and explain the study’s purpose, content, intervention, benefits, and ethical considerations. The final participants will receive the intervention for 4 weeks via a mobile application and complete pre-post surveys.

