### Intervention

#### Intervention group

DECO-MOM will be created for the Android operating system, with a user interface (UI) and user experience (UX) designed in a user-friendly and interactive manner by professionals in the field of application development. The researchers will communicate with the developers about the goals, titles, contents, strategies, animation, graphics, icons, banners, other aspects of technology, launch, updates, and sustainable testing. The web application interface will contain daily notifications, weekly feedback, and linked videos made by the researchers. The researchers will create a prototype using the application maker program “KakaoOven” and will conduct quality assurance testing through the Mobile Application Rating Scale (MARS) [22], a standardized scale for mobile application validation. The MARS contains items on basic characteristics, quality appraisal (engagement, functionality, aesthetics, and information), subjective appraisal, and purpose of using the application. It has a total of 23 items scored on a 5-point Likert scale from 1 point (inappropriate) to 5 points (very excellent). The internal consistency reliability of the MARS was demonstrated by a Cronbach’s alpha value of 0.90.

The 4-week DECO-MOM intervention will be conducted via a mobile application. A research assistant will contact participants by phone before the intervention and explain the program. The intervention will consist of (1) helping participants understand the severity of environmental toxins and susceptibility during pregnancy, (2) motivating participants to engage in environmental health behaviors and enhancing their self-efficacy, (3) enhancing perceptions of the benefits of health behaviors and working to overcome the perceived costs, and (4) empowering personal environmental behaviors and communal behaviors each week. Participants will be able to access DECO-MOM through a link or QR code provided through the KakaoTalk social networking service, which is ubiquitously used in Korea. A trained research assistant will personally contact each participant by phone every week for encouragement, and if there are open-ended questions about the application, a research assistant will provide coaching via a phone call lasting at least 10 min for each participant in DECO-MOM (Table 1).

**Table 1 Tab1:** Contents of the DECO-MOM intervention program

Sessions	Themes	Intervention format	Additional treatment

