This study will have several limitations. It will be a double-blinded randomized study; thus, the researchers will not be able contact pregnant women in person to provide social support given the need to guarantee anonymity. It is necessary to consider the risk of bias and report multiple effect estimates of the results [41]. The study population will be limited to participants capable of speaking and writing Korean in the light of cultural considerations, and to smart gadget owners; although smart gadget uptake is broad and nearly universal in Korea, economic exclusion will remain possible. Despite these limitations, this study will contribute to enhancing the environmental health conception and behaviors using a mobile application intervention, and it will serve as a valuable reference for future research.

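### The protocol claims that participants are blinded during the intervention, but women and those who coach them know the arm, and every outcome is self-reported

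*Protocol article*

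**What the plan says.** The claim appears three times in the protocol article. The abstract (Methods/Design) says: "This study presents a protocol for a double-blinded randomized controlled trial". Study design says who is blinded and when: "The researchers and participants will be double-blinded during the registration, allocation, intervention, and statistical analysis phases". The limitations paragraph of the Discussion repeats it: "It will be a double-blinded randomized study; thus, the researchers will not be able contact pregnant women in person". That last sentence goes on to limit the restriction to giving social support, for the sake of anonymity.

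The arms are described as follows.

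- Allocation: 40 women are "allocated to the intervention group (mobile application plus usual prenatal class", and 40 "will be allocated to the control group (usual prenatal class only".
- Intervention group: the app sends daily notifications and weekly feedback. In addition, "A trained research assistant will personally contact each participant by phone every week for encouragement", with coaching calls of at least 10 minutes. Table 1 lists a telephone coach in each of the four weeks.
- Control group: four two-hour classroom sessions led by a midwife on pregnancy and fetal growth, labour, postpartum care and newborn care.
- Before entry (Allocation): "The researcher will contact the pregnant women and explain the study", covering its purpose, content, intervention and benefits.

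On identity, Study design says that coding will keep participants unknown to the researchers. The same section says that "participants will complete written consent forms in face-to-face meetings with the researchers".

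Under Assessments and Outcome measurements, all scales (WEHP, WEHB, EPDS, GAD-7, EQ-5D, e-LSS) are answered by the women in an online survey.

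**The concern.** Participant blinding is a stated property of this trial that its own description of the arms rules out. That matters more here than it would with laboratory or register outcomes, because the woman who knows her arm also supplies the primary data. WEHP and WEHB ask about the perceptions and behaviours that the app and the callers set out to encourage. A woman coached for four weeks may answer as she thinks she should, whether or not her behaviour changed. Such a shift would lie in the same direction as the one-sided test in Sample size, so the test could not tell it from a true effect.

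The limitations paragraph lists loss of in-person social support as the consequence of double-blinding and says nothing of unblinded self-report. A reader or risk-of-bias assessor who took the label at face value would credit the trial with a protection that it lacks.

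**Working it through.** **Claim against design**

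1. *Can a participant be blind during the intervention?* She has been told before entry what the intervention contains. She then either has the app and receives weekly calls, or she does not. The control sessions listed have no environmental content, and no sham app, placebo content or matched calls are described. She knows her arm.
2. *Can the coaching assistant be blind?* The calls are described for DECO-MOM users and deal with questions about the app. Whoever makes them knows the arm of the woman called.
3. *Does coding of identities mask allocation?* No. A code hides who a woman is, not which arm she is in. The Discussion links double-blinding to anonymity as if one implied the other. Identities kept unknown to the researchers also sits awkwardly with consent taken face to face by the researchers, and the text does not say how both are achieved.
4. *Is there an independent assessor?* No. Every scale is self-completed.

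**Illustration of size**

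The document gives no figure for reporting bias, so the shift *b* below is an assumption.

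Inputs from Sample size: one-sided alpha 0.05; independent t-test; 58.59 ± 12.25 against 51.93 ± 12.64; 35 per group for power 0.70; 10% drop-out; 40 recruited per group.

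The plan's own figures first:

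- Pooled SD = √[(12.25² + 12.64²)/2] = 12.45, and d = 6.66/12.45 = 0.535, stated as 0.53.
- With d = 0.53, the noncentral t calculation gives 35 per group (power 0.709), as stated.
- Completers: 40 × 0.90 = 36 per arm.

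False-positive rate when the true effect is zero and app-arm scores are shifted by *b* SD:

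P(T > t₀.₉₅,₇₀), where T is noncentral t with 70 degrees of freedom and noncentrality b·√(36/2) = 4.243·b, and t₀.₉₅,₇₀ = 1.667.

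| Assumed shift b (SD) | Points (b × 12.45) | Noncentrality | False-positive rate |
|---|---|---|---|
| 0 | 0 | 0 | 5.0% |
| 0.1 | 1.2 | 0.42 | 11.0% |
| 0.2 | 2.5 | 0.85 | 21.1% |
| 0.3 | 3.7 | 1.27 | 35.0% |

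With 35 per arm, the rates for 0.1 and 0.2 SD are 10.9% and 20.7%, so the exact number of completers hardly matters.

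**The case against.** The best defence is that unblinded participants are inherent in comparing an app with a class, and that correcting the label changes no sample size, test, endpoint or allocation. That is true, and it is a reason not to claim blinding. It does not rescue a sentence that says participants are blinded during the intervention.

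Several stronger readings are tempting, and the document does not support them.

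- *The Discussion forbids researchers to meet the women, which contradicts face-to-face consent.* The sentence bars in-person contact for social support only. Consent taken before allocation would unmask nobody. The Allocation section says that the researcher contacts the women, but not that this is face to face. What remains is the tension within Study design between unknown identities and consent taken in person.
- *The protocol falsely claims that the assistants are blind.* Study design names researchers and participants, and elsewhere the text often separates researchers from research assistants. Researchers or analysts working from coded data could be masked, and nothing shows the claim for the analysis phase to be false.
- *The telephone coaching is concealed.* Table 1 lists it openly. The point is only that a conclusion about the app should name the whole package tested.
- *Bias pushes every score upward.* This is not shown. WEHP has a barriers domain, where a favourable answer may be a lower one.
- *The error rate will be 11% to 21%.* The shift is assumed, so these figures show sensitivity and are not a forecast.

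One might also suggest withholding the hypothesis from the women. That would conflict with the explanation of purpose described under Allocation, and it is not needed for the correction.

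**Conclusion.** The point holds for participants and for those who coach them: the statement of blinding during the intervention is wrong as written. Coding of identities does not supply the missing masking, and the limitations omit the consequence for self-reported outcomes. Blinding of the analysis is feasible and is not disputed.

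The amount of bias cannot be estimated from the document. The illustrative rise from 5% to about 11% to 21% rests on an assumed shift of 0.1 to 0.2 SD, no true effect and 36 completers per arm. The conclusion does not depend on it; it rests on the protocol's own description of the two arms and of how outcomes are collected. The error should be corrected before recruitment, which the Trial status section says has not begun.

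**What to change.** 1. In the abstract, Study design and the Discussion, replace the double-blind label with: *open-label for participants and intervention staff; data analyst blinded to coded arm labels until the primary analysis is complete*.
2. Treat anonymity and blinding as separate matters. State who can link codes to names, and reconcile identities unknown to the researchers with consent taken face to face by the researchers.
3. Add to the limitations that all outcomes are self-reported by women who know their arm, and that expectation or socially desirable answering could favour the app arm.
4. Word the conclusion as the effect of the app plus weekly telephone coaching, added to the usual class, on self-reported perceptions and behaviours.

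The cost is protocol wording and an analysis file with coded arm labels, with no change to sample size, visits or tests. The downside is a less favourable blinding claim.

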#### Control group

For the control group, treatment as usual will be provided via face-to-face education for 4 weeks. Each session will be conducted in the birth class room in the public health center for 2 h by a midwife. The content will be about (1) understanding pregnancy and fetal growth; (2) birth pain control, relaxation, and breathing during labor; (3) postpartum care and breastfeeding; and (4) newborn baby care. Participants will be recruited in four rounds to ensure sufficient numbers.

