### Statistical analysis

This study will use SPSS for Windows version 24.0 (IBM Corp., Armonk, NY, USA). The t-test and chi-square test will be used for homogeneity testing between the two groups. To test normality, linearity, and residual independence, the Shapiro-Wilk test will be used for the primary and secondary outcome variables. If the homogeneity test shows statistically non-significant differences between the two groups, the independent t-test will be used to compare the outcome variables between the groups. If the homogeneity test yields a statistically significant difference for even one independent variable, Analysis of covariance (ANCOVA) as a general linear model will be used to adjust the confounding variables. ANCOVA will test the following hypothesis: The intervention group would have higher scores for environmental health perceptions, behavior, psychological status, and quality of life after the DECO-MOM intervention than the control group.

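### Randomisation is blocked within two centres, but the planned t-test leaves centre out and its covariate trigger cannot bring centre in; Shapiro-Wilk is separately misused as a check of linearity and independence

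*Protocol article*

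**What the plan says.** Study design describes a 1:1 parallel randomised trial and adds: "Cluster sampling will be used with blocked randomization at two health centers". Allocation fixes the balance by city: "In total, 40 participants (20 recruited from each of the two cities) will be allocated to the intervention group", and the same 20 per city for the control group.

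Statistical analysis makes the comparison depend on a baseline homogeneity test. If that test is non-significant, "the independent t-test will be used to compare the outcome variables between the groups". ANCOVA is used only if at least one variable differs significantly between the arms. Centre is not named as a factor there, and it is not among the characteristics listed under Assessments or Other questions.

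The same section states: "To test normality, linearity, and residual independence, the Shapiro-Wilk test will be used", applied to the primary and secondary outcome variables. No other check of independence is named.

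Under Control group, usual care is face-to-face teaching by a midwife in a class room at the health centre, and "Participants will be recruited in four rounds to ensure sufficient numbers".

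**The concern.** Two separate problems sit here.

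First, the design balances the arms on centre and the analysis then discards that information. Any difference in outcome level between the two cities stays in the residual variance of the t-test, although the balance has already removed it from the difference in arm means. The calculated standard error is then larger than the true one. The trial is planned at only 70% power, so there is little to give away.

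Second, one test is assigned three jobs and can do one of them. Shapiro-Wilk assesses the shape of a distribution. It uses no information about which woman belongs to which centre or class, and none about the relation between outcome and covariate. It is also applied to the outcomes, whereas the assumptions concern model residuals. A non-significant result could be taken as support for independence when it gives none.

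**Working it through.** **1. The plan's own figure.** Sample size gives 58.59 ± 12.25 and 51.93 ± 12.64. The pooled SD is √((12.25² + 12.64²)/2) = 12.4465, and 6.66/12.4465 = 0.535, which the plan takes as 0.53. With one-sided 0.05, power 0.70 and the exact noncentral t, 35 per arm are needed (power 0.709). The stated 35 reproduces. 35/0.9 = 38.9, so 39 cover 10% dropout, and 40 are recruited. After 10% dropout, 40 × 0.9 = 36 per arm remain, with power 0.720.

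**2. Can the trigger bring centre in?** With 20 per arm per city, the chi-square for centre by arm is 0. Suppose four women per arm drop out, in the most unbalanced way: all from one city in one arm and all from the other city in the other arm. The table is then 16/20 against 20/16, and chi-square = 72 × (16×16 − 20×20)² / 36⁴ = 0.89 on 1 df, p = 0.35. The rule does not fire.

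**3. Effect of omitting centre.** Let D be the difference between centres in within-centre SDs. The protocol gives no value, so D is assumed. With centres of equal size and balanced arms:

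- SE inflation f = √(1 + D²/4)
- true one-sided alpha = 1 − Φ(1.645 f)
- power at 36 per arm = 1 − Φ(1.667 f − 0.53√18), with 0.53 read in within-centre SDs and 0.53√18 = 2.249

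| Assumed D | f | Alpha | Power, no centre term | Power, centre in model |
|---|---|---|---|---|
| 0 | 1.000 | 0.050 | 0.720 | 0.720 |
| 0.2 | 1.005 | 0.049 | 0.717 | 0.720 |
| 0.5 | 1.031 | 0.045 | 0.702 | 0.720 |
| 0.8 | 1.077 | 0.038 | 0.675 | 0.720 |

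A simulation of the planned t-test with all 40 per arm (50,000 runs per setting) agrees. For D = 0, 0.2, 0.5 and 0.8, alpha is 0.049, 0.048, 0.046 and 0.037, and power is 0.758, 0.756, 0.741 and 0.715. With centre in the model, alpha is 0.049 to 0.050 and power about 0.76 throughout. At D = 0 the extra term therefore costs nothing visible.

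**4. Can Shapiro-Wilk detect dependence?** Normal data for 80 women were simulated 4,000 times per setting and tested at 0.05. With centre differences from 0 to 1.0 SD, it rejected in 4.2% to 5.1% of datasets. With eight classes of ten and an intraclass correlation (ICC) of 0.05, 0.10 or 0.30, it rejected in 5.4%, 4.8% and 5.7%. The rejection rate stays near 5% whether or not the data are dependent.

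**5. Which way could class clustering act?** The protocol gives neither class sizes nor an ICC. Assumptions: four rounds × two centres = eight classes, five women per arm in each, ICC 0.05 to 0.10, no centre effect.

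| How classes are formed | SE of the t-test | One-sided alpha |
|---|---|---|
| Only controls clustered | 4–9% too small | 0.057–0.066 |
| Arms taught in separate classes | 9–16% too small | 0.066–0.083 |
| Arms share classes | 2–5% too large | 0.046–0.041 |

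**The case against.** The strongest reply is that the protocol calls the two cities similar on prenatal education, rural-urban character, fertility rate and particulate density, and reports no centre effect on any outcome. At D up to 0.2 SD the loss is at most 0.5% in the standard error. The error is also conservative, so it creates no false-positive risk, and with all 40 women per arm power stays above the planned 0.70 even at 0.8 SD. This stands as a limit on size. It does not show the loss to be nil, because similar fertility rates say nothing direct about perception or behaviour scores.

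The power figures also depend on reading 0.53 in within-centre SDs. The protocol takes it from overall group SDs. If it is in total SDs, the effect in within-centre units is 0.53 f. Unadjusted power at 36 per arm is then 1 − Φ(1.667 f − 0.53 f√18), about 0.73 at both D = 0.5 and D = 0.8. With centre in the model it is 1 − Φ(1.667 − 0.53 f√18), about 0.74 and 0.77. There is then no shortfall against plan, but adjustment still gains.

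Model detail is often left to an analysis plan. Here, however, the article itself fixes both the test and the rule for admitting covariates, so the point corrects a stated rule.

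Three stronger readings are tempting and are not supported:

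- A reader might infer that the intervals are certainly too wide. That needs a prognostic centre, and class clustering could push the other way.
- A reader might infer that the Shapiro-Wilk error itself distorts the intervals. It does not; it only leaves dependence unexamined.
- A reader might infer from *cluster sampling* that the trial is cluster-randomised and lacks a design effect. With 20 women per arm in each city, the centre is not the randomised unit. The term can describe how women are sampled, so it is loose wording and not a shown contradiction.

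**Conclusion.** The point holds in two parts.

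The analysis omits the factor used to balance the arms, and the stated trigger will in practice never restore it. The direction is certain only if centre predicts the outcome: the standard error is then too large and the test conservative. The size rests on an assumed centre difference. It is about 0 to 3% in the standard error and under two power points for differences up to 0.5 SD, and 8% and between four and five power points at 0.8 SD (36 per arm, 0.53 in within-centre SDs). This is a modest loss of efficiency, not a threat to validity, but avoiding it costs almost nothing.

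The use of Shapiro-Wilk for linearity and residual independence is wrong under any assumption about centre. Its practical weight comes from the taught classes. Dependence there would go undetected, and whether it makes the standard error too small or too large turns on how the arms share classes, which the protocol does not say.

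**What to change.** Recruitment had not begun according to Trial status, so all of this can be settled beforehand.

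- For every outcome, replace the t-test with a prespecified linear model containing treatment and centre as a fixed factor, plus the baseline score where one is collected. E-learning satisfaction has no pre-test, so its model has treatment and centre only.
- Remove the homogeneity test as the condition for adjustment.
- Limit Shapiro-Wilk to normality of the model residuals, and check linearity with residual plots.
- Justify independence from the design, stating how classes are formed and whether the arms share them. Heteroscedasticity-robust standard errors are no substitute, because they address unequal variance and not correlated observations.
- Reword *cluster sampling* as individual randomisation in blocks, stratified by health centre.

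The cost is wording, one degree of freedom for centre and one more for the baseline score. No extra women or data are needed.

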### Assessments

The pre- and post-test will be assessed just before and after the intervention. For both groups, the pre- and post-test will be conducted via online survey using a Naver Form distributed personally through the KakaoTalk messenger. The online survey will take 10 min. After the pre- and post-test, an online gift worth 5 dollars will be provided to the participants. The survey will take 10 min, and a gift worth 5 dollars will be provided to the participants after the pre- and post-test. The questionnaire will contain items on participants’ general characteristics (age, gestational age, gravidity, parity, the presence of a living baby, past medical history), environmental perceptions, environmental behavior, depression, anxiety, quality of life, and e-learning satisfaction. The general characteristics will be surveyed only in the pre-test, and e-learning satisfaction will be surveyed only in the post-test (Table 2).

**Table 2 Tab2:** Study assessments and time points

	WEHP	WEHB	EPDS	GAD-7	EQ-5D	e-LSS
Pre-test	x	x	x	x	x	
Post-test	x	x	x	x	x	x

Primary outcomes: WEHB (Women’s Environmental Health Behavior) and WEHP (Women’s Environmental Health Perception)

Secondary outcomes: GAD-7 (General Anxiety Disorder-7), e-LSS (e-Learning Satisfaction Scale), EPDS (Edinburgh Postpartum Depression Scale), and EQ-5D (European Quality of life 5-Dimension)

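### The two centre assistants who recruit women also run the randomisation, which does not secure allocation concealment and conflicts with the blinding claim and with the Allocation section

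*Protocol article*

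**What the plan says.** All references are to the protocol article.

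- **Who recruits and randomises (Study design).** Both groups are to be "recruited from registration lists for birth education by two trained research assistants at health care centers using SPSS for Windows", and the purpose of the software in that sentence is "to conduct randomization".
- **Method (Study design).** "Cluster sampling will be used with blocked randomization at two health centers". The block size is not given. The Allocation section fixes 20 women per arm in each city.
- **Blinding (Study design).** "The researchers and participants will be double-blinded during the registration, allocation, intervention, and statistical analysis phases". Identities are also to be coded.
- **Second account of enrolment (Allocation).** "If pregnant women agree to participate in the study, nurses at the centers will obtain their mobile phone numbers and refer them to the researcher". Explanation of the study then falls to the researcher. Study design adds that the researchers take signed consent in person.
- **Programme call (Intervention group).** "A research assistant will contact participants by phone before the intervention and explain the program".
- **Baseline (Assessments).** "The pre- and post-test will be assessed just before and after the intervention". The pre-test is an online form that each woman completes herself.
- **Status (Trial status).** Recruitment has not started.

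**The concern.** Randomisation protects against selection only if the person who decides whether and when to enrol a woman cannot know or foresee her arm. A person who produces a sequence in SPSS can read it. If that person also works through the registration list, more motivated women could be approached when the next slot is the app arm, or the study could be presented differently by arm.

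Motivation is directly relevant to self-reported environmental perceptions and behaviours, and it is not among the recorded baseline characteristics. The homogeneity tests and covariate adjustment, on which the Discussion relies to deal with selection bias, therefore cannot be counted on to remove it.

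The second risk concerns the pre-test. If a woman already knows her arm when she fills in the form, her answers may shift. The Statistical analysis section lets baseline tests decide between the t-test and ANCOVA, so a shifted baseline could also influence which analysis is run.

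**Working it through.** **1. The plan's own figure.** Inputs from Sample size: means 58.59 and 51.93, SDs 12.25 and 12.64, one-sided 5%, power 0.70.

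- Pooled SD = √[(12.25² + 12.64²)/2] = 12.4465.
- d = (58.59 − 51.93)/12.4465 = 0.535, stated as 0.53.
- With d = 0.53 the noncentral t distribution gives 35 per group (power 0.709), as stated.
- 35/0.90 = 38.9, so 39; the plan recruits 40.

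The sample size reproduces. This point does not depend on it, except that 35 per arm is used in step 4.

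**2. The sections side by side.**

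| Step | Study design | Allocation, Intervention group, Assessments |
|---|---|---|
| First contact | two centre assistants, from registration lists | centre nurses, who refer to the researcher |
| Explanation | not stated | the researcher |
| Consent | the researchers, in person | person not stated |
| Randomisation | the same two assistants, in SPSS | person not stated |
| Programme call | not stated | a research assistant, before the intervention |
| Pre-test | not stated | just before the intervention |

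No section separates the holder of the sequence from the people who enrol. No section places consent or the pre-test before or after assignment, or the pre-test before or after the programme call.

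**3. Predictability without the list (illustration).** Assumptions: women are randomised one by one in permuted 1:1 blocks, and the observer knows the block size and all earlier assignments. For block size b = 2m, the expected number of correct best guesses is m + [4^m / C(2m, m) − 1]/2.

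| Assumed block size | Expected correct guesses | Share |
|---|---|---|
| 2 | 1 + (4/2 − 1)/2 = 1.50 | 75% |
| 4 | 2 + (16/6 − 1)/2 = 2.83 | 71% |
| 6 | 3 + (64/20 − 1)/2 = 4.10 | 68% |
| 8 | 4 + (256/70 − 1)/2 = 5.33 | 67% |
| 40 (one block per centre) | 20 + (7.976 − 1)/2 = 23.49 | 59% |

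Chance is 50%. For whoever holds the list it is 100%.

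**4. Effect of selection on the error rate (illustration).** Assume that selection moves the outcome mean in the app arm by δ SD with no true effect. At 35 per arm the critical value is 1.667 (68 degrees of freedom) and the shift in the test statistic is δ√(35/2) = 4.183δ. The one-sided error is then approximately 1 − Φ(1.667 − 4.183δ).

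| Assumed δ | 1.667 − 4.183δ | One-sided error |
|---|---|---|
| 0.05 | 1.458 | 7% |
| 0.1 | 1.249 | 11% |
| 0.2 | 0.831 | 20% |
| 0.3 | 0.412 | 34% |

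The documents give no value for δ, and steps 3 and 4 are not linked: a guess rate does not translate into a particular shift.

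**The case against.** The best defence is that the article never says allocation is open. It claims blinding at allocation and coded identities, and a condensed article may leave the concealment mechanism to the full protocol. On the Allocation account, moreover, the nurses and the researcher who meet the women are not the assistants who randomise. This stands in part. The absence of a described mechanism is no finding. What the article does state is that one pair of on-site assistants recruits and randomises, and that arrangement is the difficulty. The blinding sentence names researchers and participants. If the assistants count as researchers, it contradicts their role; if they do not, it does not cover the people who recruit. The Allocation account helps only once the two descriptions are reconciled.

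Four stronger readings are tempting and are not supported:

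- **That allocation is definitely not concealed.** No section says so. The described roles fail to secure concealment, which is a smaller statement.
- **That the pre-test is taken after allocation.** Just before the intervention fixes no order relative to randomisation. Consent, pre-test, assignment, call, intervention is compatible with every sentence.
- **That groups are formed from the list before consent.** The Allocation section makes referral conditional on the woman's agreement, and nothing places randomisation earlier than that.
- **That a contaminated pre-test spoils the ANCOVA covariate.** The Statistical analysis section does not name the pre-test score as the covariate; it speaks of confounding variables.

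The guess rates also matter only if women are randomised singly. The Control group section says recruitment comes in four rounds, and the article does not say whether assignment is by woman or by round.

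**Conclusion.** The point holds in a limited form. As described, the roles of the two centre assistants do not protect allocation concealment. They conflict with the blinding claim in the same section, if the assistants are part of the research team, and with the enrolment route in the Allocation section. Baseline answers influenced by knowledge of the arm are possible, because the order of steps is open, but they are not shown.

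The figures show what could be at stake and do not estimate bias in this trial. They rest on assumed block sizes, known earlier assignments, one-by-one randomisation and assumed shifts of 0.05 to 0.3 SD. The change should be made before recruitment begins, because neither selection on unmeasured motivation nor a baseline shifted by knowledge of the arm can be reliably repaired in the analysis.

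**What to change.** 1. Have each centre's sequence generated and held, with varying block sizes, by a current team member who does not recruit, consent or coach at that centre. The other centre's assistant would do, if each centre has one. Block sizes that sum to 40 keep the planned 20 per arm in each centre; they should not be disclosed to those who enrol.
2. State one order: consent, online pre-test submitted, assignment released, programme call, intervention.
3. Reconcile Study design, Allocation, Intervention group and Assessments, so that one account says who approaches, explains, takes consent, randomises and coaches. Bring the blinding sentence into line with it.

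If actual practice already separates these roles, correcting the text is enough. The cost is one task moved between existing staff and a form link sent slightly earlier. No visits, questionnaires or participants are added.
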